## 2. Materials and Methods

### 2.1. Study Setting and Design

To ensure the completeness and quality of reporting, we referred to the SPIRIT (Standard Protocol Items: Recommendations for Interventional Trials) [9] guidelines as well as Thabane and Lancaster’s [10] guidance on how to report protocols of pilot and feasibility trials. The protocol was registered in the ClinicalTrials.gov PRS database (Registration number: NCT06270420, https://clinicaltrials.gov/study/NCT06270420, accessed on 22 February 2024). This single group, pre-post longitudinal pilot study will be conducted within the HosmartAI research project (EU Horizon 2020, research and innovation program—grant agreement No 101016834). The trial will last twenty months and will be carried out at the San Camillo IRCCS Hospital (Venice, Italy), within which a smart rehabilitative room (HR) will be created. This room will feature rehabilitation devices complemented by smart-home sensors and actuators developed by VIMAR SpA (Marostica, Italy), all of which send data to a cloud system (Kloud) created by Khymeia Group (Padua, Italy). The purpose of this setup is to develop an innovative solution to monitor various activities that patients can perform autonomously or under therapists’ supervision. This solution aims to assist clinicians in monitoring patients within the hospital, identifying potential risks, and ensuring adherence to therapy protocols. Throughout the pilot phase, stakeholders involved will be closely observed using a persona-based approach, providing valuable insights into the behaviors of therapists and patients, thus enabling the analysis and exploration of the extension of active patient monitoring to the home environment.

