### 2.3. Intervention

Subjects were enrolled among hospitalized patients based on the pre-defined inclusion criteria. The identification of eligible subjects was conducted through notification by the Clinical Research Unit at San Camillo Hospital. Subsequently, researchers from the HosmartAI project will enroll and evaluate (T0) the patients, after which they will commence their experimental treatment in the HR room, in addition to their regular daily conventional rehabilitation session. The experimental treatment will be tailored to the subjects’ therapeutic needs and will run for three weeks, comprising 15 one-hour sessions each, conducted five days a week. The specialized devices targeting balance, manual dexterity, and limb functionality, as described in the study setting section, will be utilized during these sessions. Pre-treatment (T0) and post-treatment (T1) assessments will be conducted using validated clinical scales and tests to determine therapy effects. Additionally, device-specific evaluation systems will be employed to assess treatment outcomes. A qualitative analysis will ascertain technology usability, acceptability, and user satisfaction. All assessments and treatments will be administered by qualified physiotherapists. Figure 1 illustrates the participants’ timeline.

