### 2.5. Sample Size

The study aims to recruit subjects from IRCCS San Camillo Hospital’s Neurorehabilitation Department. With an average occupancy of 60 beds per week, it is estimated that four eligible subjects are admitted monthly. Given a 20-month trial period, the target sample size was set at 80 subjects. To evaluate the reliability of our study’s results, a retrospective (post-hoc) power analysis was conducted using G*Power 3.1.9.6 software (Heinrich-Heine-University Düsseldorf, Germany). With a two-tailed test, a moderate effect size (Cohen’s d) of 0.5, an alpha level of 0.05, and a total sample size of 80, the analysis yielded a calculated statistical power of 0.99. This suggests a strong probability of detecting the expected effects and highlights the potential dependability of our findings.

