### 2.6. Data Collection and Analysis Plan

Patient data, including clinical and demographic information, will be collected and inputted into treatment devices. A unified cloud platform will consolidate information from SH&BA devices and patient clinical data stored across devices. Data from HR sensors will gauge patient therapy adherence.

Descriptive analysis will be initially conducted on the enrolled subjects’ sample. For each demographic and clinical variable, we will consider the mean, standard deviation [23], absolute frequencies (n), and percentages (%). For each mode of clinical treatment delivery (i.e., depending on the physiotherapist/patient ratio), pre-treatment (T0) and post-treatment (T1) motor performance values will be compared using either Student’s t-test for paired data or the Wilcoxon test, depending on the data distribution, which will be assessed with the Kolmogorov–Smirnov test. To assess the presence of a statistically significant difference in motor recovery in relation to the type of treatment model, the motor outcomes of the patients will be compared by means of parametric or non-parametric independent sample comparison tests (i.e., Student’s t-test for independent data or the Mann–Whitney test), depending on the data distribution. To identify the patient profile that best fits each therapy model, regression models will be utilized, with the type of therapy model as the dependent variable, and assessment scales and anamnestic variables as predictor variables. To define the satisfaction, usability and technology acceptance and clinical profile of patients accessing technological therapy, tests for customer satisfaction will be utilized. The statistical significance is set at *p* < 0.05. Data analysis will be conducted using the free statistical software R Studio, version 4.0.3 [24].

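### Section 2.6 names Student's t-test for comparing motor recovery between delivery modes whose sizes and spreads are not fixed; Welch's test should be named instead

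*Protocol article*

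**What the plan says.** The design is one cohort measured twice (section 2.1): "This single group, pre-post longitudinal pilot study will be conducted within the HosmartAI research project". Section 2.6 nevertheless divides that cohort by how therapy is delivered: "For each mode of clinical treatment delivery (i.e., depending on the physiotherapist/patient ratio". It then plans two kinds of motor analysis: a paired T0 versus T1 comparison within each mode, and a comparison between models by "independent sample comparison tests (i.e., Student’s t-test for independent data or the Mann–Whitney test), depending on the data distribution". Normality is to be judged with the Kolmogorov–Smirnov test, and the significance level is 0.05.

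The article does not give the number of modes, the patients per mode, the rule by which a patient comes to a mode, or the SD of motor change. It does not mention equal variances, pooling or Welch's test. On the intervention, section 2.3 says only: "The experimental treatment will be tailored to the subjects’ therapeutic needs".

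**The concern.** Student's two-sample test estimates one common variance from both groups. When the groups differ in size, the larger group dominates that estimate. If the smaller group is the more variable one, the standard error is too small and the test rejects too often. If the larger group is the more variable one, the standard error is too large and the test rejects too rarely. A switch driven by distribution shape does not detect either case, because two normal samples can have very different spreads.

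Equal spread cannot be taken for granted here. Eligible diagnoses range from stroke to peripheral neuropathy (section 2.2). Several scales are bounded (section 2.4), so patients near a ceiling have little room to change. Section 2.6 also plans a regression to find which patient profile suits which therapy model, so the authors themselves allow that modes may hold different patients. These facts do not show that spreads differ. They show that the plan has no basis for assuming they are equal.

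At stake is whether the 5% level holds for the between-model motor comparisons.

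**Working it through.** **1. The plan's own power figure.** Section 2.5 states: "With a two-tailed test, a moderate effect size (Cohen’s d) of 0.5, an alpha level of 0.05, and a total sample size of 80", and "the analysis yielded a calculated statistical power of 0.99". For a paired t-test with n = 80 and d = 0.5, the noncentrality is 0.5 × √80 = 4.47 on 79 degrees of freedom, and the power is 0.993. The stated figure is reproduced. For an independent-samples test at 40/40 with the same d, the power is 0.598. The 0.99 therefore belongs to the pre-post comparison and says nothing about group sizes or spreads in the between-model comparison.

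**2. Inputs for the error check.**
- From the article: total N = 80, nominal level 0.05. The test is taken as two-sided, as in section 2.5.
- Assumed, because the article is silent: two modes; splits 40/40, 30/50, 27/53, 20/60 and 16/64; SD ratio r (smaller group over larger) from 0.5 to 2; normal change scores with equal means.

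**3. Large-sample formula.** With group sizes n₁ (smaller) and n₂, and SDs r and 1:
- true variance of the mean difference: T = r²/n₁ + 1/n₂
- variance that the pooled test uses, on average: P = [(n₁−1)r² + (n₂−1)]/78 × (1/n₁ + 1/n₂)
- actual level ≈ 2 × [1 − Φ(1.96/√(T/P))]

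Worked cases:
- 20/60, r = 2: T = 4/20 + 1/60 = 0.2167; P = (76 + 59)/78 × 0.0667 = 0.1154; √(T/P) = 1.370; 1.96/1.370 = 1.430; level 15.3%.
- 16/64, r = 2: T = 0.2656; P = 123/78 × 0.0781 = 0.1232; √(T/P) = 1.468; level 18.2%.
- 16/64, r = 0.5: T = 0.03125; P = 66.75/78 × 0.0781 = 0.0669; √(T/P) = 0.684; level 0.4%.
- 40/40, r = 2: T = P = 0.125; level 5.0%.

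**4. Simulation.** 100,000 runs per scenario, equal means, nominal 5%:

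| Split | Student, r = 0.5 | r = 1 | r = 1.5 | r = 2 |
|---|---|---|---|---|
| 40/40 | 5.0% | 4.9% | 5.0% | 5.1% |
| 30/50 | 2.4% | 5.1% | 7.5% | 9.3% |
| 27/53 | 1.9% | 5.0% | 8.6% | 11.1% |
| 20/60 | 0.9% | 4.9% | 10.6% | 15.2% |
| 16/64 | 0.5% | 5.0% | 12.0% | 18.0% |

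The simulation agrees with the formula. Across the same scenarios Welch's test lies between 4.85% and 5.11%.

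**5. Price of Welch's test when variances are equal.** Simulated power at d = 0.7: 76.8% (Student) against 75.3% (Welch) at 20/60, and 84.7% against 84.4% at 30/50. The losses are 1.5 and 0.3 points.

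**The case against.** The strongest reply is that the pooled form is an inference. The article never mentions equal variances, and it names R. There the standard two-sample t-test call runs Welch by default (checked in version 4.3.3, not in the 4.0.3 that the article cites). A condensed article may also leave the variance form to its analysis plan. This is why the point is worded conditionally. It does not remove the point, because the text names a specific test, introduced as an exhaustive choice of two. An analyst who follows the words and one who follows the software default could get different p-values from the same data.

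Four stronger readings are tempting, and the document does not support them:

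- *That the error is two to three times 5%.* This needs roughly a 1:3 split with the smaller mode 1.5 to 2 times as variable, or a similar combination. The article gives neither figure. Equal groups show no distortion, and the opposite pattern makes the test conservative.
- *That the modes will probably be unequal.* No group sizes are stated. Tailoring to need does not say how patients reach a mode, and it does not imply unequal numbers or spreads. The sizes are simply not fixed.
- *That lack of randomisation breaks the test.* It does not in itself change the error rate. Its consequence is confounding of mode with patient characteristics, which Welch's test leaves untouched.
- *That the Mann–Whitney option is an error.* The plan asks about a difference in recovery and does not say that a rank result will be read as a difference in means. For an ordinal outcome such as the 0–5 Functional Ambulation Categories, a rank test is a reasonable choice.

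It is also fair to say that little hangs on this comparison. The primary aim in section 2.4 is productivity, and motor change is secondary.

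**Conclusion.** The point holds as a minor, conditional one. Section 2.6 names a test whose usual form assumes equal variances, for groups whose sizes and spreads the article leaves open. If the pooled form is applied, its level could lie anywhere from about 0.5% to 18% over the range tried, and at 5% if the groups are equal in size. That range rests on assumed two-group splits, assumed SD ratios and normal change scores. It shows how sensitive the test is and does not predict what this study will see. Welch's test is close to 5% in every scenario, so naming it removes the dependence at almost no cost.

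**What to change.** In section 2.6, for the parametric between-model comparison, replace Student's t-test for independent data with Welch's unequal-variance t-test on the T0–T1 change. Report the mean difference in change with its Welch 95% CI. The Mann–Whitney alternative can stay as written.

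The cost is a change of test name in software the plan already uses. If variances are equal, about 1.5 power points are lost at 20 vs 60 and 0.3 at 30 vs 50 (both at d = 0.7). The change does not adjust for differences in patient characteristics between modes, so a between-model result would still need to be read with that confounding in mind.

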Future implications include profiling patient suitability for this organizational model and its transferability to other rehabilitation settings. However, it is important to acknowledge the limitations of this study, such as the need for expert physiotherapists and potential enrolment complexities, as well as the inherent constraints of pilot studies, including small sample size, a lack of control groups, and limited generalizability. Nevertheless, despite these limitations, the study’s findings are expected to inform and facilitate similar technology implementations in various rehabilitation medical centers. One of the most significant implications is the potential for personalized therapeutic approaches which could concurrently enhance operational efficiency. Specifically, the implementation of SH&BA therapies within technological group treatments for neurological subjects holds promise for augmenting therapy quantity, thereby potentially improving clinical outcomes [28]. This envisaged scenario would unfold alongside resource optimization efforts, aiming to enhance the precision and reliability of collected data and administered therapies, while also striving to mitigate errors. Furthermore, enhancing the patient experience is indeed a significant aspect. The integration of smart-home technologies provides the potential to enhance the overall patient experience during the rehabilitation process. By offering a more comfortable and familiar environment for therapy, it enables greater autonomy and control throughout the healing journey. Moreover, the consideration of patients’ social interaction during group therapy sessions, which also contributes to clinical improvement, further underscores the holistic approach to patient care [29]. Lastly, the remote monitoring capabilities of these systems could expand access to rehabilitation services, particularly for patients in remote or disadvantaged areas.

Disseminating these results nationally and internationally underscores the project’s significance. Efforts to address these limitations and refine the methodology will be crucial in maximizing the impact and applicability of the study’s findings.

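### The regression meant to find the patient profile that best fits each therapy model describes who received each model, not who does better under it

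*Protocol article*

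**What the plan says.** Section 2.6 of the protocol article gives the aim and the method in one sentence. The aim is "To identify the patient profile that best fits each therapy model". The method is that "regression models will be utilized, with the type of therapy model as the dependent variable, and assessment scales and anamnestic variables as predictor variables".

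A therapy model is a delivery mode. Section 2.6 introduces the pre-post comparison with "For each mode of clinical treatment delivery (i.e., depending on the physiotherapist/patient ratio". Section 2.1 describes the design: "This single group, pre-post longitudinal pilot study will be conducted within the HosmartAI research project". No random or rule-based allocation to delivery mode is described, and no number of patients per mode is given. Section 2.3 adds: "The experimental treatment will be tailored to the subjects’ therapeutic needs".

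One other planned analysis links therapy model to recovery: "the motor outcomes of the patients will be compared by means of parametric or non-parametric independent sample comparison tests". It contains no patient characteristics. Section 3 says: "Future implications include profiling patient suitability for this organizational model".

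**The concern.** Fit is a question about benefit: does the difference in motor recovery between delivery modes depend on what the patient was like at the start? That is a model-by-characteristic interaction in a regression whose dependent variable is recovery. The planned regression runs the other way and estimates the probability of having received a model, given the patient's characteristics. Without randomisation, that probability may reflect patient needs, staff judgement, staffing or scheduling.

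At stake is the reading of the result. A significant predictor would be reported as part of the profile that fits a model, when it shows only that such patients were found there more often. A real difference in benefit could go unseen if placement did not follow the same characteristic.

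**Working it through.** **The plan's own figure.** The document gives no figure for this regression. Its one power figure (section 2.5) is 0.99 for N = 80, d = 0.5, two-tailed alpha 0.05. As a paired t-test, the noncentrality is 0.5 × √80 = 4.47 on 79 degrees of freedom, and power is 0.993. The figure is reproduced, but it concerns the pre-post comparison and says nothing about profiling.

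**Step 1: what the planned model can see.** Let m be the therapy model received (0 or 1) and x a standardised baseline characteristic. With baseline predictors, the planned model is logit P(m = 1 | x) = a₀ + a₁x. T1 does not appear, so a₁ cannot respond to who benefits.

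**Step 2: what the fit question needs.** T1 = b₀ + b₁x + b₂m + b₃(x × m) + error. Differential benefit is b₃. No planned analysis contains this term.

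**Step 3: simulation.** From the documents: n = 80 and alpha 0.05. Assumed, because the documents are silent: two models, one predictor, logistic regression, T0–T1 correlation r = 0.7 (residual SD √(1 − 0.49) = 0.714), 1,500 runs, and the values of a₁ and b₃ below.

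| Placement on x (log OR per SD) | True b₃ (SD per SD) | Planned regression flags x | Interaction test flags b₃ |
|---|---|---|---|
| 1 | 0 | 97–98% | 5% |
| 0.5 | 0 | 55% | 5% |
| 0 | 0.6 | 4–5% | 94% |
| 1 | +0.6 or −0.6 | 97–98%, coefficient about 1.05 both times | not needed here |

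A second set of 1,000 runs used change scores and b₃ = ±0.8. The planned regression flagged x in 97–98% of runs at +0.8, 0 and −0.8. The interaction test rejected in 86–90% at ±0.8 with the mean estimate of the right sign, and in 5.5% at zero.

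**Step 4: T1 scores among the predictors.** The text does not limit assessment scales to T0. If T1 is normal given x and m, with slope b₁ on x, a model shift of b₂ + b₃x and residual variance σ², then Bayes' rule adds [(b₂ + b₃x)(T1 − b₁x) − (b₂ + b₃x)²/2]/σ² to the log-odds of the model. The T1 main effect carries the average difference b₂. Differential benefit needs an x × T1 product term, and a main-effects regression has none. In simulation with T1 added and placement unrelated to x, a true b₃ of 0.6 left x flagged in 4% and T1 in 5% of runs. With placement on x and no differential benefit, x was still flagged in 79%.

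**Step 5: precision of the replacement.** With an even split, the standard error of b₃ is about 0.714 × √(1/40 + 1/40) = 0.16, so the 95% interval is about ±0.31. Simulated power is about 94% for 0.6, 42% for 0.3 and 24% for 0.2 (one set of runs gave 21%). For 0.6 it is 78% with a 20/80 split, and 64% if only 40 patients have the relevant scale.

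**The case against.** Several points on the other side are sound.

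- **Rank in the plan.** Section 2.4 makes service productivity the primary aim and lists motor function, quality of life and user experience as secondary. Profiling is in neither group, so no listed outcome changes if this regression is mis-specified. This point stands and limits the severity.
- **A descriptive reading.** The next sentence of section 2.6 speaks of the clinical profile of patients who access technological therapy, so the regression may be meant only to characterise users. On that reading the model is adequate and the stated aim is wrong, so the text still has to change.
- **T1 scores as predictors.** If they enter, the coefficients no longer describe placement alone. That is correct, but step 4 shows that main effects still do not test who benefits.
- **Assumed sizes.** Placement strength, correlation, split and interaction come from no part of the document. The contrasts in the table show how the two models behave and measure nothing about this trial.

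Two stronger readings are tempting. A reader might infer that the output will simply reproduce therapists' allocation habits. The documents do not say who sets the delivery mode or how. Tailoring in section 2.3 concerns the treatment, and the physiotherapist/patient ratio could equally follow staffing or scheduling. A reader might also infer that the profile will be presented as evidence of suitability and carried to other centres. Section 3 lists suitability and transferability as future implications of one organisational model and does not refer to this regression. The link is plausible but not stated.

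An unseen analysis plan does not remove the point, because the protocol already fixes the dependent variable and the predictors.

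**Conclusion.** The point holds as a mismatch between a stated aim and a stated method. The regression describes who received each therapy model and cannot show who does better under it at any sample size. With baseline predictors this follows from the form of the model and needs no simulation. The extension to T1 main effects rests on step 4.

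It should be fixed, but it is not critical to the study: the analysis is neither a primary nor a listed secondary outcome of a single-group pilot. A reader might take the 97–98% against 5%, or the 94% power, as forecasts for this trial. They are not, because the documents give none of the inputs except n and alpha.

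**What to change.** Choose the question and match the text to it.

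1. **For the fit aim**, make the T1 motor score (a named scale) the dependent variable. Include T0 score, therapy model, a short prespecified list of baseline predictors and the model-by-predictor interactions. Report the interactions with confidence intervals, labelled exploratory and non-randomised, since an interaction can also be confounded by how delivery mode was set.
2. **Keep the existing regression** only as a description of who received each model, state that its predictors are T0 values, and reword its aim accordingly.

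If the investigators want description only, the second change is enough. The cost is wording: T0 and T1 scores, delivery mode and history are already to be collected. The downside is the imprecision in step 5, so a null interaction at n = 80 should not be read as evidence that all profiles fit equally well.
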